# Community-based trial of annual versus biannual single-dose ivermectin plus albendazole against *Wuchereria bancrofti* infection in human and mosquito populations: study protocol for a cluster randomised controlled trial

**DOI:** 10.1186/s13063-017-2196-9

**Published:** 2017-10-02

**Keywords:** Lymphatic filariasis, Biannual treatment, Twice-yearly treatment, Increased treatment frequency

## Abstract

**Background:**

The Global Programme for the Elimination of Lymphatic Filariasis (GPELF) has been in operation since the year 2000, with the aim of eliminating the disease by the year 2020, following five to six rounds of effective annual mass drug administration (MDA). The treatment regimen is ivermectin (IVM) in combination with diethylcarbamazine (DEC) or albendazole (ALB). In Ghana, MDA has been undertaken since 2001. While the disease has been eliminated in many areas, transmission has persisted in some implementation units that had experienced 15 or more rounds of MDA. Thus, new intervention strategies could eliminate residual infection in areas of persistent transmission and speed up the lymphatic filariasis (LF)-elimination process. This study, therefore, seeks to test the hypothesis that biannual treatment of LF-endemic communities will accelerate the interruption of LF in areas of persistent transmission.

**Methods:**

A cluster randomised trial will be implemented in LF-endemic communities in Ghana. The interventions will be yearly or twice-yearly MDA delivered to entire endemic communities. Allocation to study group will be by clusters identified using the prevalence of LF. Clusters will be randomised to one of two groups: receiving either (1) annual treatment with IVM + ALB or (2) annual MDA with IVM + ALB, followed by an additional MDA 6 months later. The primary outcome measure is the prevalence of LF infection, assessed by four cross-sectional surveys. Entomological assessments will also be undertaken to evaluate the transmission intensity of the disease in the study clusters. Costs and cost-effectiveness will be evaluated. Among a random subsample of participants, microfilaria prevalence will be assessed longitudinally. A nested process evaluation, using semi-structured interviews, focus group discussions and a stakeholder analysis, will investigate the community acceptability, feasibility and scale-up of each delivery system.

**Discussion:**

It is expected that this study will add to the existing evidence on the need for alternative intervention strategies for the elimination of LF in Ghana and in other African countries that are facing similar challenges or are at the beginning of their LF-elimination programmes.

**Trial registration:**

ClinicalTrials.gov, ID: NCT03036059. Registered on 26 January 2017.

Pan African Clinical Trials Registry, ID: PACTR201702002012425. Registered on 23 February 2017.

**Electronic supplementary material:**

The online version of this article (doi:10.1186/s13063-017-2196-9) contains supplementary material, which is available to authorized users.

## Background

Lymphatic filariasis (LF) is a debilitating, mosquito-borne, nematode infection that has been targeted for elimination as a public health problem by 2020. It affects 120 million people in 73 countries where 1.46 billion people are at risk of acquiring the infection through infectious mosquito bites. In 2000, the World Health Organisation, in collaboration with pharmaceutical companies and endemic country governments, launched the Global Programme to Eliminate LF (GPELF). Ivermectin (IVM) in combination with diethylcarbamazine (DEC) or albendazole (ALB) remain the drugs available for the large-scale control of LF [1]. These drugs only temporarily clear microfilariae (mf) without killing all adult worms [2], and it is assumed that a reduction in population mf load will lead to a simultaneous reduction, or even interruption, of transmission [3–5]. It is, therefore estimated, that five to six rounds of mass drug administration (MDA) are required to eliminate the disease. From 2000 to 2014, LF MDA included a cumulative total of 5.62 billion treatments delivered to more than one billion people at least once [6, 7]. Many countries including Ghana have since undertaken between 8 and 15 consecutive annual rounds of MDA in several implementation units without interrupting transmission. In Ghana, where the MDA coverage rates have been more than the required 65%, 29 sentinel sites with persistent residual infections have been identified, with microfilaria prevalence rates of above 1% [8]. Previous studies [9] revealed high prevalence of LF (13% antigen prevalence and 4.6% mf prevalence) in two communities in a district with persistent LF transmission. In these communities, individuals positive for LF were treated and followed at 3-month intervals for 1 year. The results showed a decline in prevalence after treatment, followed by an increase 6 months after treatment (Table 1).

**Table 1 Tab1:** Number of positives and parasite loads at different time points (Unpublished data – [name])

	Dec 2014 (pre treatment)	3 months post treatment	6 months Post treatment	9 months Post treatment	12 months Post treatment
ICT positives	48	17/48 (35.4%)	26/48 (54.2%)	23/33 (69.7%)	15/30 (50%)
mf positives	17/48 (35.4%)	4/48 (8.3%)	4/48 (8.3%)	3/33 (9.1%)	2/30 (6.7%)

*ICT i*mmunochromatographic test, *mf* microfilariae

With the failure to interrupt the transmission of LF in some areas following the recommended years of MDA, alternative and effective MDA regimens and strategies are needed if the GPELF is to achieve the goals of global elimination. Simonsen and colleagues, therefore, recommended treatment to be given at shorter intervals – perhaps every 6 months [2]. Further, a study reported that in villages which were hyperendemic for onchocerciasis, after some 14 years of biannual treatment with IVM, no *Wuchereria bancrofti* could be detected, while in adjacent villages a prevalence of around 3% was found [10]. The elimination of onchocerciasis in some countries in the Americas has been attributed to the use of twice-yearly treatment regimens [11, 12]. Even though there are no studies that explicitly compare the effects of once yearly versus twice-yearly treatment in onchocerciasis control [13], this provides some evidence that biannual treatment may be effective in the control of LF in areas with persistent transmission. In Ghana, the onchocerciasis programme undertakes twice-yearly treatment with IVM in onchocerciasis (river blindness) hyper-endemic districts and it is believed that the use of twice-yearly treatment in these onchocerciasis endemic districts may have contributed to the absence of LF in these districts. However, there is the absence of data to ascertain these observations, since onchocerciasis treatment started in 1996, 4 years prior to the mapping of LF prevalence in the country. Other drugs, such as DEC, have also been shown to have marked effects on mf reduction [3, 14, 15]. However, research to test alternative treatment regimens (including single, high doses of ALB or biannual treatment schedules) have been recommended [1], and concrete evidence is required to inform policy and the need for alternative strategies.

Reviewing the literature using PubMed, Web of Science, Google and other online journals, revealed that there is a lack of information on the use of the twice-yearly treatment strategy for the control of LF. A number of studies have proposed the need for twice-yearly treatment for the control of LF [2, 8, 16]. From these studies, it is clear that increasing the MDA frequency is a considerable global research priority. Two randomised control trials in Mali [17] and Malawi [18] that assessed the dosage and frequency of treatment for LF control have been identified, and have shown the usefulness of increased dosage and frequency of IVM and ALB in suppressing *W. bancrofti* microfilaraemia levels in populations. These, together with the evidence from onchocerciasis studies [10] and anecdotal reports indicate the benefits of the increased treatment frequency. These studies however have limitations in the number of participants randomized and focused on LF control in the general endemic population, compared to the current study in areas with persistent transmission, that face the additional challenge of potential drug resistance by *W. bancrofti*, as a result of the prolonged period of treatment. The impacts of the interventions have also not been assessed in the vectors, especially when different vector species exhibit different transmission processes. This current study will, therefore, assess the impact, feasibility and acceptability of the twice-yearly treatment for the control of LF in both human and vector populations, and will be useful in the implementation of the twice-yearly treatment in countries in Africa that are yet to start MDA or are at the early stages of their implementation programmes.

To advance knowledge for the control of LF in areas with persistent transmission, the trial proposed herein will address the following questions: (1) Can a twice-yearly treatment with IVM and ALB eliminate residual LF infections in areas with persistent transmission? and (2) Can the implementation of the twice-yearly treatment accelerate the interruption of transmission of the disease in these areas? This study will test the hypothesis that biannual treatment of LF-endemic communities will accelerate interruption of LF in areas of persistent transmission in Ghana.

### Study aims and objectives

The primary objective of this trial is to interrupt the transmission of LF with a twice-yearly treatment with IVM and ALB. The secondary objectives are to assess the impact of the twice-yearly treatment on transmission of parasite in areas of persistent transmission and evaluate the cost-effectiveness of a twice-yearly treatment versus the current yearly treatment based on IVM and ALB. The study will also include process and economic evaluations to assess the feasibility and implementation of the twice-yearly treatment, which will guide scale-up similar interventions in other settings in Africa. The more detailed study objectives are:To quantify the impact of twice-yearly versus yearly community treatment (treatment strategies and delivery systems) in reducing parasitological and entomological LF transmission indices in ‘hotspot’ areasTo evaluate the costs and cost-effectiveness of twice-yearly treatment in reducing LF transmissionTo assess the extent to which the twice-yearly treatment is acceptable to the community and feasible, given the health system capacity, and can be easily scaled-up elsewhereTo assess the impact of IVM and ALB treatment on other intestinal and soil-transmitted helminthes (STH)

### Study design

This is a phase-4 study of an approved drug, with the aim to delineate additional information for its optimal usage and efficacy. It is designed as a cluster randomised, open-label trial with two study arms, with the ultimate aim of comparing the endpoint results in the intervention versus control arm. A community cluster randomised trial in different settings in Ghana will evaluate the impact and cost-effectiveness of twice-yearly and yearly MDA. The primary outcome is the prevalence of LF. This outcome is selected because it is the prevalence of LF that determines the level of on-going transmission (both parasitological and entomological) and the need to implement Transmission Assessment Surveys and stop MDA [19]. Allocation to study group will be by villages, identified through programme reports, and by disease-control officers in the study districts. The mf prevalence in all communities will be re-evaluated, based on nucleopore filtration of 1 ml of night-blood collected from study participants, prior to assignment to study groups.

The two study groups are:Control group: annual MDA. Clusters (with members aged 5 years and above) will receive 400 μg/kg IVM + 400 mg ALB from trained community drug distributors (CDDs), as part of the ongoing national MDA programmeExpanded frequency group: annual MDA with 400 μg/kg IVM + 400 mg ALB, followed by an additional MDA 6 months later. The drugs will be provided by the national programme and administered by the CDDs, following the structures of the National MDA programme

### Study outcomes and measurements

The primary outcome, the prevalence of LF infection, will be measured through cross-sectional parasitological surveys conducted at baseline and at 12, 24 and 30 months’ follow-ups. Figure 1 presents a flowchart of the study design. The timing of the final follow-up survey will take into account differences in time since treatment of the annual and biannual treatment groups at 24 months. The time point assessments at 12, 24 and 30 months will allow us to evaluate changes in the primary study outcome in the intervention and control groups over time. For secondary outcomes, a subsample of individuals from the clusters in each of the study groups will be followed longitudinally for 2.5 years in order to better understand the transmission dynamics of LF and to estimate key parameters for mathematical modelling of transmission dynamics and treatment impact. The impact of treatment on other STHs (roundworm (*Ascaris lumbricoides*), whipworm (*Trichuris trichiura)*, and the hookworms (*Ancylostoma duodenale* and *Necator americanus*) and any other species identified) will also be assessed. A nested process evaluation, using semi-structured interviews, focus group discussions (FGDs) and a stakeholder analysis, will investigate the community acceptability, feasibility and participation in the twice-yearly drug administration. The local and regional health system structures and processes will be evaluated to determine the feasibility to scale-up the interventions.

**Fig. 1 Fig1:**
[figure not shown]
Flowchart of study activities

## Methods

The publication of this research protocol follows the SPIRIT (Standard Protocol Items for Randomised Trials) recommendations [20]. For the SPIRIT Checklist see Additional file 1, and for the SPIRIT Figure see Fig. 2. Table 2 provides an overview of the trial characteristics.

**Fig. 2 Fig2:**
[figure not shown]
Standard Protocol Items for Randomised Trials (SPIRIT) Figure – Schedule of enrolments, interventions and assessments

**Table 2 Tab2:** Trial registration data

Data category	Information
Primary registry and trial identification number	ClinicalTrials.gov, ID: NCT03036059
Date of registration in primary registry	26 January 2017
Secondary identifying numbers	Ghana Health Service Ethics Review Committee: 04112/2016 Noguchi Memorial Institute for Medical Research IRB: CPN 062/16-17
Source(s) of monetary or material support	EDCTP grant TMA 2015 CDF - 976
Primary sponsor	Noguchi Memorial Institute for Medical Research
Contact for public queries	[name]
Contact for scientific queries	[name], [name], [name]
Public title	Twice Yearly Treatment for the Control of LF
Scientific title	Cluster Randomised Community-based Trial of Annual Versus Biannual Single-dose Ivermectin Plus Albendazole Against Wuchereria Bancrofti Infection in Human and Mosquito Populations
Country of recruitment	Ghana
Health condition(s) or problem(s) studied	Lymphatic filariasis
Interventions	400 μg/kg ivermectin + 400 mg albendazole tablets given once or twice a year
Key inclusion and exclusion criteria	Inclusion criteria: residency in endemic community for at least 12 months; willingness to provide informed consent/assent; willingness to donate blood (per the protocol) Exclusion criteria: recent residents (<12 months) in the study districts; inability to give informed consent due to illness, serious medical problems or refusal to participate in the study; pregnancy; children below the age of 5 years
Study type	Interventional allocation: randomised Masking: no masking, open label
Date of first enrolment	19 May 2017
Target sample size	1440
Recruitment status	Recruiting
Primary outcome(s)	Change from baseline prevalence of lymphatic filariasis at 12, 24 and 30 months
Key secondary outcome(s)	Longitudinal assessment of transmission dynamics of lymphatic filariasis. Evaluation of community acceptability of twice-yearly treatment. Feasibility of scale-up of twice-yearly treatment

### Study population

This study will be undertaken in the Western Region of Ghana, which lies within the high rain forest vegetation climate zone of the West African subregion, with strands of mangroves. The highest mean temperature is 34 °C while the lowest is 20 °C. Relative humidity is very high, averaging between 75% to 85% in the rainy, and 70% to 80% in the dry seasons. Rainfall is experienced throughout the year with the highest monthly mean occurring around May and June (http://mofa.gov.gh/site/?page_id=1778). The main economic activities in the region are agriculture and fishing. The region has a commercial capital, Takoradi and an administrative capital, Sekondi, located about a 3.5-h drive away from Accra, the capital of Ghana. Besides the main administrative capitals, the communities in the districts are predominantly rural. The region is one of the highest endemic zones in the country [21].

The sites selected are areas that have had 13–15 rounds of yearly treatment, without interrupting transmission of LF. The study areas selected are also among the highest endemic communities (zones) in the country. Undertaking the study in these sites, therefore, provides the opportunity to assess the impacts of the intervention.

The study will be carried out in 18 clusters in the Western region of Ghana. Communities were selected following a review of the Neglected Tropical Disease Programme (NTDP) sentinel and spot check site monitoring data, as well as recommendation from the District Health Management Team (DHMT). Based on these, 18 communities were selected, distributed into three districts in the Western Region of Ghana (Fig. 3). In these districts, the persistent transmission of LF has been reported following several rounds of MDA [8] and previous studies also indicated inaccuracies in the treatment coverage data reported [22].

**Fig. 3 Fig3:**
[figure not shown]
Study districts and communities

### Sensitisation and recruitment

Key stakeholders will be involved in the study and its design. Prior to implementation, meetings will be held with the NTDP, and at each study site, where key stakeholders (chiefs, community leaders and study participants) will be sensitised about the study objectives, interventions, evaluation procedures, and requested to provide input as well as the need for their participation in the study. Community meetings will be held to describe the purpose of the study, the interventions, the evaluation procedures to be followed, and the risks and benefits associated with participation. Individuals will have the opportunity to ask questions for which answers will be provided by the research team.

Consent for the intervention will be provided at the community level with the option for individuals to opt out. Community drug distributors (CDDs) used by the NTDP will number all houses and update their community registers through coordination with the chiefs and village elders. Using a random number generator in Excel, households will be selected until the sample size for each village is attained. Subsequently, households selected for inclusion into the study will be visited by field staff, for consenting and recruitment into the study. In each household visited, written informed consent to conduct the household-level questionnaire will be sought from the household head. Individual-level consent will be sought from selected individuals, 18 years old and above (either for themselves or their children) and written assent sought from children aged 12–17 years.

### Survey procedures

At each house, household heads will be interviewed to collect information on household characteristics and other information during household visits. Data on sex, age, occupation, participation in previous MDAs and duration of residence will be recorded. Information on mosquito nets or other barriers present in the house will also be recorded.

CDDs will update their treatment registers with a full record of all individuals who have received treatment. To augment these data, population-based coverage surveys, using multistage clustering sampling [23], will be carried out among a random subsample of communities. In each cross-sectional survey, 100-μl finger-prick blood samples will be collected (from selected individuals) during the day and tested for circulating filarial antigen (CFA) using the Alere Filariasis Test Strips (FTS) [24]. Individuals positive for LF antigen will be followed for night-blood collection, for mf detection [25]. To enhance the sensitivity of microfilaria detection, the nucleopore filtration method using 1 ml of blood will be employed. Two-milliliter venous blood samples will be collected in heparinised capillary tubes at night between 9 p.m. and 2 a.m., and used in the nucleopore filtration method. The night collection will be done between these periods because *W. bancrofti* shows nocturnal micofilariae level periodicity, which peaks within 9 p.m. to 2 a.m. Arrangements will be made with the study participants on the timing for the blood collection. Ten percent of all samples will be evaluated for quality control by a supervisor.

IgG4 antibody testing using the Wb123 assay will be used in a subset of study participants (individuals positive for LF antigen and children aged 5–10 years), and the results evaluated together with the antigen and microscopy results. The evaluation of the test in individuals positive for LF antigen is done to identify new from existing infection, while the selection of children 5–10 years is done to assess the usefulness of the antibody testing for Transmission Assessment Surveys, used for determining the criteria for stopping MDA [19]. However, while the presence of IgG4 may reflect exposure to infective parasite (antibody responses develop before patent infection and, as such, positive responses may be suggestive of recent filarial exposure), antibodies take a long time (sometimes years) to normalise after treatment [26], and detection of antibody response in populations that have been treated only shows that these have been exposed at some point. Pilot assessments in a limited population of individuals treated with IVM and ALB pointed to implementation and interpretation challenges [27]. The inclusion of the Wb123 assay in the study thus provides an opportunity to further evaluate its usefulness when undertaking impact/evaluation assessments. As such, the usefulness of this test on the overall outcome will be considered carefully in the data analysis.

In addition, samples will be stored (for up to 10 years) for future studies at the Noguchi Memorial Institute for Medical Research (NMIMR), including the detection of potential drug-resistance alleles and genome sequence analysis to investigate the genetic structure of *W. bancrofti* populations. All members of the study teams will be appropriately trained in the study objectives and procedures. Standard operating procedures (SOPs) will be developed, used to guide all field and laboratory activities. Supervisors will make regular visits to the field to monitor the activities.

Future use of the samples for purposes not specified in the Information Document for Participants will have to be approved by the Ethics Committee/Review Boards in Ghana which approved this study. The use of these samples by external parties to the current study (whether for research specified in the Information Document or beyond) will be based on a Material Transfer Agreement.

### Longitudinal surveys

Individuals who are positive for LF antigen and microfilaria (at baseline) will be followed longitudinally to help quantify the transmission dynamics of LF. They will be asked to provide blood samples 1 month following treatment. Two milliliters of venous blood will be collected in heparinised capillary tubes at night between 9 p.m. and 2 a.m. The collected samples will be transported to the laboratory and analysed. Subsequently, they will be revisited at 3, 6, 9 and 12 months post treatment and asked to provide a sample, which will be examined for the presence of *W. bancrofti* mf [21, 22]. They will also be requested to provide stool samples for the examination of STH infections.

The study team will also conduct household visits to assess the extent of non-compliance to treatment and factors associated with non-compliance [28–33]. The assessment of non-compliance will be based on short, standardised questions, as well as a review of the community drug distribution register.

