### Secondary outcomes

A subsample of 80 individuals from the following clusters: low (1%), medium (2–4%) and high (>5%) LF prevalence; in each of the study groups will be followed longitudinally for 2.5 years in order to better understand the transmission dynamics of LF, and to estimate key parameters for mathematical modelling of transmission dynamics and treatment impact. Both the presence and intensity of *W. bancrofti* mf will be assessed at 3, 6, 9 and 12 months post treatment. Information on covariates that influence *W. bancrofti* mf transmission in humans, such as use of bed nets, will be measured at each of these endpoints.

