#### Analysis strategy

Each of our study outcomes, i.e. prevalence and intensity of *W. bancrofti* mf, will be considered separately during the analysis. Loss to follow-up was taken into consideration during our sample size calculation. Therefore, regardless of the number of incomplete observations, we expect to end up with no less than 58 complete observations per community at the end of the study.

A panel of individual line plots for the study participants would be used in the assessment of within-person variability. Since the assumptions of likelihood are violated by the effect of within-group and within-subject clusters in longitudinal data, in assessing the transmission dynamics of LF infection, the measured covariates will be regressed separately on both the prevalence and the intensity of infections using a quasi-likelihood method, i.e. generalised estimating equations, which uses an association matrix instead of the diagonal matrix employed by the generalised linear models. As part of the model validation, the point-referenced residuals of the provisional models will be assessed for spatial autocorrelation. The results of this assessment would help to determine if unmeasured/unobserved factors in the study areas play relevant roles in the transmission dynamics of LF infections. Using classical geostatistical concepts, our final model would be adjusted for both the effects of the measured and unobserved factors.

For entomological endpoints, infection rates will be determined, using the polymerase chain reaction (PCR) [40] and LAMP [41] methods. The results will be analysed using the poolscreening software by Katholi and colleagues [42, 43].

The findings and data from this study will be used to develop a mechanistic model, which describes the variability in treatment responses in populations. This will be implemented into an already available and well-established transmission dynamic model for LF (LYMFASIM) [44, 45], which will then be used to systematically explore the consequence of twice-yearly treatment on the long-term impact of MDA and elimination prospects. LYMFASIM simulates the spread of *W. bancrofti* in a human community and the impact of control measures, with the advantage of accounting for a variety of parameters specific to the population of interest and output predictions [45, 46].

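### The longitudinal cohort is restricted to baseline microfilaria-positives in one section and is an unrestricted subsample in the others; the restricted version cannot show new infection or reach 58 people per community

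*Protocol article*

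**What the plan says.** All references are to the protocol article.

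- **Abstract, Methods:** "Among a random subsample of participants, microfilaria prevalence will be assessed longitudinally".
- **Study outcomes and measurements:** a subsample of individuals from the clusters in each study group, followed for 2.5 years to understand transmission dynamics and to estimate parameters for the transmission model. No infection criterion is given.
- **Longitudinal surveys:** "Individuals who are positive for LF antigen and microfilaria (at baseline) will be followed longitudinally to help quantify the transmission dynamics of LF". These people give blood 1 month after treatment, and then: "Subsequently, they will be revisited at 3, 6, 9 and 12 months post treatment and asked to provide a sample".
- **Secondary outcomes:** the cohort is given as "A subsample of 80 individuals from the following clusters: low (1%), medium (2–4%) and high (>5%) LF prevalence; in each of the study groups". They "will be followed longitudinally for 2.5 years in order to better understand the transmission dynamics of LF, and to estimate key parameters". Mf presence and intensity are assessed at 3, 6, 9 and 12 months post treatment. Again there is no infection criterion.
- **Analysis strategy** (under Secondary outcomes): mf prevalence and mf intensity are each analysed, and "we expect to end up with no less than 58 complete observations per community at the end of the study".

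**The concern.** Longitudinal surveys and Secondary outcomes give the same purpose and the same 3, 6, 9 and 12 month visits, so a field team would take them as the same cohort. They select different people. At the 4.6% mf prevalence quoted in the Background, a rule that admits only mf-positives leaves out about 95% of those whom a random subsample would include.

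The choice decides what can be estimated. The cohort is meant to supply mf prevalence, transmission dynamics and model parameters. If everyone is mf-positive at entry, nobody is at risk of a first mf-positive result, so the cohort yields no incidence, and its prevalence describes treated positives rather than the community. The per-community numbers expected under Analysis strategy would also be out of reach. Membership is set at baseline, and Trial status says recruitment is under way. If uninfected people are not enrolled at baseline, their baseline mf status cannot be recovered later.

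**Working it through.** **Inputs**

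- 58 per cluster required, 37% non-response and loss, 80 per cluster recruited, 18 clusters, 1440 in total (Sample size calculation).
- 45 households × 5 members = 225 per cluster (Cluster randomisation).
- Mf prevalence 4.6% and antigen prevalence 13% in two earlier study communities (Background).
- Prevalence in the hotspot districts 1% to 18.2%, marker not stated (Sample size calculation). Reading all of it as mf favours the protocol.

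**The plan's own figure.** 58 × 1.37 = 79.46, rounded up to 80; 80 × 18 = 1440. Both figures reproduce. But multiplying by 1.37 does not offset a 37% loss: 80 × 0.63 = 50.4. Keeping 58 would need 58 / 0.63 = 92.06, that is 93. The 58 complete observations per community are therefore not secured even in the full sample.

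**Size of an mf-positive cohort.** Expected mf-positives per village = number sampled × mf prevalence, before any loss:

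| Mf prevalence | 80 sampled per village | 225 sampled per village |
|---|---|---|
| 1% | 0.8 | 2.3 |
| 4.6% | 3.7 | 10.4 |
| 18.2% | 14.6 | 41.0 |

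Over 18 villages with 80 sampled in each, the totals are about 14, 66 and 262.

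To find 58 mf-positives in a village, mf prevalence would have to be 58 / 80 = 72.5%, or 58 / 225 = 25.8%. In the most favourable cell (225 sampled, 18.2%), the binomial chance of 58 or more is 0.3%, before loss.

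**The figure of 80 under Secondary outcomes.** The text does not say whether 80 is a total, a number per arm, or a number per band and arm.

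- As a total, mf-positives reach it at 80 / 1440 = 5.6%, or 80 / 4050 = 2.0%.
- Per arm, at 80 / 720 = 11.1%, or 80 / 2025 = 4.0%.
- Per band and arm, assuming three clusters in each, the 1% band yields 3 × 0.8 = 2.4, or 3 × 2.25 = 6.8.

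The shortfall against 80 therefore depends on the reading; the shortfall against 58 per community does not.

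**What can be observed.** With Y = 1 for mf-positive, every member starts at Y = 1. Moves from 1 to 0, and later back to 1, are visible. A first move from 0 to 1 after baseline is not.

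**Related loose ends.** The listed visits run to 12 months post treatment, while follow-up is 2.5 years. Table 3 treats the expanded-frequency group every 6 months, so 9 and 12 months after one round are 3 and 6 months after the next. The bands, low (1%), medium (2–4%) and high (>5%), leave values below 1%, between 1% and 2%, and from above 4% up to and including 5% unassigned, and the marker is not named.

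**The case against.** The strongest defence is that only Longitudinal surveys stands apart. A reader might count three incompatible definitions, but the Abstract's random subsample can be the same thing as a sample drawn within the prevalence bands of Secondary outcomes. Longitudinal surveys also has a 1-month visit and stool samples that Secondary outcomes lacks, so it may describe a nested subgroup of positives. That is possible, but the article does not say so, and the shared purpose and visits point the other way.

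The 58 comes from the all-participant sample size, and no section promises 58 mf-positives. That stands: the shortfall arises only if Longitudinal surveys defines the cohort analysed.

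A reader might infer that an mf-positive cohort says nothing about transmission, or that its prevalence can only fall. Neither is supported. Reappearance and intensity are measurable and useful for modelling variation in treatment response. In Table 1, antigen positivity among people followed after treatment went from 35.4% to 54.2% to 69.7% at 3, 6 and 9 months, on changing denominators. The section itself claims only to help quantify transmission dynamics.

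A reader might also infer regression-to-the-mean bias in the treatment effect. Clusters are randomised and both arms are selected by the same baseline rule, so regression to the mean and natural clearance act in both. Only an uncontrolled before–after claim would be exposed.

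The visit list can be read as recurring after each annual round, and the different time since last dose at 9 and 12 months is part of the randomised contrast, so neither is a firm error. Nor can one say what share of villages falls between bands. That would need mf as the marker, 80 sampled and one common true prevalence, and the text does not require every village to be classified.

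**Conclusion.** The conflict is real and unreconciled: baseline antigen- and mf-positives in one section, against a subsample with no infection criterion in three others. Followed as written, Longitudinal surveys gives a cohort that can describe clearance, reappearance and intensity, but not new infection from baseline or community mf prevalence. It would hold roughly 0.8 to 14.6 people per village with 80 sampled, or 2.3 to 41.0 with 225, against an expected 58.

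This rests on the two sections meaning the same cohort and on the 1% to 18.2% range being mf prevalence; if it is antigen prevalence, mf-positives are fewer. The point concerns secondary outcomes and the modelling inputs, and should be put right.

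**What to change.** - State one cohort: the random subsample of the Abstract, Study outcomes and measurements, and Secondary outcomes, drawn whatever the baseline infection status. Say whether 80 is a total, per arm, per band or per cluster.
- Keep baseline mf-positives as a separately labelled clearance and intensity subgroup, not used for prevalence or incidence.
- State that the 58 per community does not apply to that subgroup, and correct it for the full sample: either about 50 expected from 80, or 93 recruited to keep 58.
- Reconcile the 12-month visit list with the 2.5-year follow-up. Carry months since the last treatment round as a covariate. Because it is part of the randomised contrast, also show the arm comparison without it.
- Make the prevalence bands contiguous and name the marker.

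**Cost.** Mostly wording, since the subsample is already planned. The real cost is night-blood sampling of mf-negative members. Secondary outcomes already implies it, but Survey procedures limits night blood to antigen-positives in the cross-sectional surveys. At the Background's 13% antigen prevalence, about 87% of a random subsample would be antigen-negative, so most of the night sampling would fall on people not now scheduled for it.
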